### Sample size

Assuming that 30% of patients in the polyurethane arm will show healing of PrU-II at 8 weeks, an alpha risk of 5%, a beta risk of 20% with bilateral contrast and a loss to follow-up of 15%, 410 individuals will be required in each treatment arm to detect a ≥10% difference in healed ulcers [22,23].

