### Secondary outcome variables

#### Efficacy

*Changes in the basal PUSH scale,*[24-27] ulcer area (in cm [2]) at the end of treatment, exudates and tissue type. This information will be collected weekly until the end of the study or until the PrU-II heals.

*Changes in ulcer area in cm*[2] will be measured using ImageJ software [28,29]. Two photographs, taken at the beginning and end of treatment (8 weeks or when the wound heals), will be evaluated by members of the expert panel committee. A <10% difference in ulcer area measured by two evaluators will be considered ‘agreement’ and the final measure will be the average of these measurements. A ≥10% difference in ulcer area between the two evaluators will be considered ‘disagreement’, requiring measurement by a third investigator, with the final measure being the average of the two closest measurements. This method has been used in other studies to evaluate changes in ulcer area [30].

Cost-effectiveness (partial cost-effectiveness evaluation): cost per proportion of healed ulcers and cost per treated patient. In both treatment arms, the healing process registry must reflect information regarding dressings and material used, including cost per unit dressing, cost per secondary dressing, additional material used for each patient (e.g. saline, gauzes, globes, tubing, syringes), and time spent by each nurse performing these procedures (mm:ss).

Dressing convenience (patient comfort) [31-33] will be evaluated by both patients and study nurses using Likert scales ranging from 1 (worst outcome) to 5 (best outcome) to assess the following measures:

*Patients:* adherence to dressing; pain at dressing removal; pain during application of dressing; overall comfort; and time during the healing process

*Study nurses:* adherence to dressing; ease of applying the dressing; ease of removing the dressing; absorption by the dressing; perilesional skin condition, as assessed by erythema; perilesional skin condition, as assessed by maceration; and time during the healing process.

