### Withdrawal criteria

Patients will be removed from the trial if any of the following conditions are met:

•Infection and/or progression of PrU-II

•Disease progression, requiring discontinuation of the investigational product treatment regimen or study requirements.

•An adverse event (AE) that requires discontinuation of the investigational product or study procedures.

•Voluntary withdrawal

•Loss of follow-up

Protocol deviations will be registered. In case of a serious protocol deviation, the research team will assess the possibility of withdrawing the patient from the study.

Study discontinuations must be registered in the CRF, and, where possible, tests and procedures usually performed at the final visit (visit 8 or end of study) should be carried out. Patients who withdraw due to AEs must be followed until the end of the study (8 weeks), and if necessary until AE resolution.

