Recording of concomitant medications

Recording of adverse events

This study will last 8 weeks (8 visits) or until the ulcer heals, whichever comes first. The protocol for Visit 8 can include 3 different situations:

1. *PrU-II heals before week 8 (visit 8).* If complete healing is observed at an earlier visit, the nurse will perform the activities described for that Visit plus those described for Visit 8.

2. *PrU-II does not heal by week 8 (visit 8)*. The nurse will perform all the activities described for Visit 8.

3. *The patient presents some withdrawal criteria before week 8 (Visit 8).* The nurse will perform all the activities described for the earlier visit, as well as those described for Visit 8.

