### Statistical analysis

#### Intention to treat analysis (ITT)

All statistical calculations will be based on ITT analysis, including all patients randomized, whether treated or not, and including all patients who have withdrawn prematurely. This approach reduces any bias that may occur when participants not receiving assigned treatments are excluded from analysis. All tests will be two-sided and α-values of 0.05 will be considered statistically significant.

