#### Comparative analysis

In a bivariate analysis, a χ^2^ test will be used to assess whether the percentage of healed PrU-IIs differs significantly in the two treatment arms. Mean changes in PrU size will be compared using Student’s t-tests for normal distributions or the Mann-Whitney U test against the usual null hypothesis (non-normal distributions): (initial area-final area)*100/initial area). In addition, 95% confidence intervals will be calculated to assess the clinical significance of treatment.

A logistic regression model adjusted for potential confounders will be performed when patients are not equally distributed in both treatment arms. Relative and absolute risk reduction and number needed to treat, defined as the estimated number of ulcers needed to be treated with the chosen dressing for one additional ulcer to be healed will be estimated, along with their corresponding 95% CIs.

Time to healing in the two treatment arms will be calculated by the Kaplan-Meier method and compared using the log-rank test. A Cox regression model of proportional risks will be used when the models require adjustment for any statistically significant baseline variable.

Finally, a partial economic evaluation will be performed, including direct costs such as number of dressings used per patient, additional dressings used, materials used, labor cost per cured ulcer and further treatment cost. The overall differences in mean costs and effects between treatments will be calculated using Student’s t-tests.

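### The t-test of mean costs makes no allowance for cost records cut short at unhealed exit, so cost per treated patient is understated and the comparison is biased if exits differ between arms

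*Protocol article*

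**What the plan says.** All points are from the protocol article.

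- **Cost measures** (Secondary outcome variables, Efficacy): "cost per proportion of healed ulcers and cost per treated patient".
- **Source of cost data** (same section): in both arms "the healing process registry must reflect information regarding dressings and material used", together with unit costs and nurse time. The Work plan schedules this registry at study visits and adds a record of each dressing change between visits.
- **Cost items** (Comparative analysis): the direct costs include "materials used, labor cost per cured ulcer and further treatment cost".
- **Method** (Comparative analysis): "The overall differences in mean costs and effects between treatments will be calculated using" Student's t-tests. For time to healing, the same section names Kaplan-Meier, the log-rank test and, if needed, Cox regression.
- **Analysis set** (Intention to treat analysis): all calculations are on this basis, "including all patients randomized, whether treated or not, and including all patients who have withdrawn prematurely".
- **Removal** (Withdrawal criteria): "Patients will be removed from the trial if any of the following conditions are met". The conditions include infection or progression of the ulcer, disease progression, adverse events, voluntary withdrawal and loss. Only patients who withdraw because of adverse events must be followed to week 8.
- **Early exit** (Work plan, third situation for Visit 8): "The nurse will perform all the activities described for the earlier visit, as well as those described for Visit 8".
- **Expected loss** (Sample size): "a loss to follow-up of 15" per cent, not split by arm.

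**The concern.** Two kinds of patient leave before week 8, and their recorded totals mean different things. A patient whose ulcer heals has no further dressing cost, so the total is complete. A patient removed or lost with an open ulcer goes on generating cost that the registry does not capture. A plain t-test on recorded totals in all randomized patients does not separate the two. The plan does use a method that handles censoring for time to healing over the same weeks, but not for cost.

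Some exits are treatment failures, since infection and progression are removal criteria. A dressing that fails more often, or earlier, would then show a lower recorded cost per treated patient. Cost-effectiveness is part of the hypothesis in the Discussion paragraph of the abstract, so the sign of this difference will be read.

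The Comparative analysis section also counts the cost of further treatment, but neither the cost list under Efficacy nor the visit lists in the Work plan shows where that item is collected after exit.

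**Working it through.** **The plan's own figure.** The plan gives no figure for costs. Its sample size reproduces: 30% v 40%, two-sided 5%, 80% power gives 356 per arm, and 356 × 1.15 = 409.4, rounded up to 410. Here it serves only to set the standard error.

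**Inputs from the plan.** Healing by week 8 of 30% (foam) and 40% (hydrocolloid, 10 points more); 15% loss; 8 weeks; 410 per arm.

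**Assumptions, not in the plan.** Constant healing and exit hazards, exits unrelated to healing, one cost unit per week under treatment in both arms, and the exit splits tried below.

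**Complete cost.** Healing hazard h = −ln(1 − p)/8, which is 0.0446 (foam) and 0.0639 (hydrocolloid). Mean weeks at cost = (1 − e^(−8h))/h, which is 6.73 and 6.26. The true saving is 0.46 weeks.

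**Recorded cost.** The exit hazard e solves e/(h + e) × (1 − e^(−8(h + e))) = proportion who exit. The recorded mean is (1 − e^(−8L))/L with L = h + e.

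| Exits, foam / hydrocolloid | Recorded mean, foam | Recorded mean, hydrocolloid | Recorded saving | Shift from 0.46 |
|---|---|---|---|---|
| 15% / 15% | 6.15 | 5.70 | 0.45 | −0.02 |
| 20% / 10% | 5.95 | 5.89 | 0.06 | −0.41 |
| 10% / 20% | 6.35 | 5.50 | 0.84 | +0.38 |
| 17.5% / 12.5% | 6.05 | 5.80 | 0.25 | −0.21 |
| 12.5% / 17.5% | 6.25 | 5.60 | 0.65 | +0.18 |

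At 15% / 15% each arm's mean is too low by 8.6% (foam: 1 − 6.15/6.73) and 9.0% (hydrocolloid: 1 − 5.70/6.26), but the difference hardly moves.

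**Size against sampling error.** With no variation in weekly cost, the standard deviations of weeks at cost are 2.32 and 2.57, so the standard error is √((2.32² + 2.57²)/410) = 0.17, and 0.4/0.171 = 2.3. If weekly cost varies between patients with coefficient of variation c, independently of duration, the variance in each arm is (1 + c²)·E[M²] − E[M]², where M is weeks at cost and E[M²] is 50.6 (foam) and 45.9 (hydrocolloid).

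- c = 0.5: variances 18.0 and 18.1, standard error 0.30, and 0.4/0.297 = 1.3.
- c = 1.0: variances 56.0 and 52.5, standard error 0.51, and 0.4/0.514 = 0.8.

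**Effect on the test.** A separate simulation took equal healing (35%) and equal true cost in both arms, 410 per arm and 2,000 repetitions. Exit hazards were set to give 10% v 20% exits by week 8 in the absence of healing. Recorded means were 6.19 v 5.87, so the arm with more exits looked 5.2% cheaper. The t-test rejected in 19.5% of runs at c = 0.5 and in 10.0% at c = 1.0. With 15% in both arms it rejected in 5.7% and 4.1%, close to the nominal 5%.

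**Cost per healed ulcer.** Under the same hazards the observed proportion healed is h × recorded mean, so the ratio is 1/h whatever the exits: 1/0.0446 = 22.43 (foam) and 1/0.0639 = 15.66 (hydrocolloid), in every row of the table. Exits cut cost and observed healing together. This cancellation fails when exits are informative. If those removed for infection or progression would not have healed by week 8, their exit lowers recorded cost without lowering the number healed, and the ratio falls.

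**The case against.** The strongest reply is that the article is silent on incomplete costs. It does not say that truncated totals count as complete, and missing-data rules are commonly left to a full protocol or analysis plan that is not shown. The point about silence stands, and a reader who infers that the plan declares partial costs complete goes beyond the text. But the article does fix the analysis set, the removal rules and the test. Applied as stated, they put truncated totals into the comparison, so the concern is with a named method and not only with a missing detail.

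Four further limits also stand.

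- A reader might infer that costs cannot be completed for anyone who leaves early. That is too broad. Patients withdrawn for adverse events are followed to week 8, although the article does not say whether dressing costs are recorded then, and the further-treatment item may cover some later cost.
- A reader might infer that both cost measures are biased. Cost per healed ulcer is unchanged when exits are unrelated to healing.
- The only exit figure in the plan is an overall 15%. Nothing in it predicts an imbalance, and with balanced exits the difference is nearly unbiased.
- The figure of 2.3 standard errors sets variation in weekly cost to zero. Realistic variation makes the shift smaller relative to sampling error.

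**Conclusion.** The concern holds in a limited form. As the plan is written, cost per treated patient is understated in each arm, by about 9% at 15% exits under constant hazards and equal weekly cost. The difference between arms is biased in favour of whichever arm has more, earlier or costlier unhealed exits, and negligibly so if exits are balanced. An assumed 10-point imbalance shifts the difference by about 0.4 treatment-weeks against a true 0.46, enough nearly to erase it or nearly to double it. In standard errors the shift is about 2.3, 1.3 or 0.8 for a coefficient of variation of weekly cost of 0, 0.5 or 1.0. The exit splits and the cost variation are assumptions. If patients removed for infection or progression cost more afterwards than the average unhealed patient, the understatement is larger than shown.

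This should be corrected, but it touches a secondary outcome in a partial economic evaluation. The primary chi-square comparison of healing is unaffected.

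**What to change.** In the Comparative analysis section:

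1. Define cost per patient over a fixed 8-week horizon, with zero dressing cost after healing and cost treated as censored at unhealed exit.
2. Replace the plain t-test of recorded totals by a censoring-adjusted mean cost per arm, either weekly partitioned or inverse-probability-weighted, using arm and last PUSH score, with a bootstrap confidence interval for the difference.
3. Add a sensitivity analysis that carries each unhealed exit to week 8 at the arm's mean weekly cost for unhealed patients, and at a higher weekly cost for those removed for infection or progression.
4. Reconcile the further-treatment cost item with the cost list under Efficacy and the visit lists in the Work plan, and state whether costs are recorded while adverse-event withdrawals are followed. The item should not simply be deleted, because it is the one listed component that could cover cost after exit.

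Steps 1 to 3 need only analysis wording and some extra programming, since dated dressing changes, materials, nurse time and weekly PUSH scores are already recorded. The price is a slightly wider confidence interval and reliance on exits being explained by arm and last PUSH score. That is doubtful for removals due to infection or progression, which is why step 3 includes the higher-cost scenario.

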### Ethics

The trial has been approved by the Balearic Island Ethic Committee. It will be performed by qualified nurses. The rights and welfare of patients will be respected throughout the trial. All involved patients will be informed, verbally and in writing, of the trial objectives, risks and possible benefits. Signed informed consent form will be required from each patient. The trial will respect and follow the standards of good clinical practice enshrined in the Declaration of Helsinki [34,35].

## Discussion

PrUs are an important health problem, not only due to their high incidence and prevalence but to their effects on health and quality of life. Of these lesions, about 40% have been categorized as stage II [36,37].

PrU-II treatment consists mainly of the application of polyurethane and hydrocolloid dressings, which are recommended and part of habitual clinical practice. However, little is known about the relative efficacy of these two types of dressings.

Among available data, highlights a recent systematic review evaluating the effectiveness of modern dressings in the treatment of venous ulcers [21] found that hydrocolloid dressings were the most common type, evaluated in 27 of 45 (60%) clinical trials (CTs). Most of these CTs compared hydrocolloid dressing with other types of dressings or compared different types of hydrocolloid dressings.

The review included a meta-analysis of four CTs, involving 311 patients, [38-41] comparing the effectiveness of hydrocolloid and polyurethane foam dressings for venous ulcers, with the primary outcome being the total number of healed ulcers in 8–12 weeks. However, that analysis found no statistically significant difference in the healing rates with dressings (pooled relative risk (RR) 0.98; 95% CI, 0079 to 1.22).

Similarly, another meta-analysis of three CTs [23,42,43] comparing the effectiveness of hydrocolloid dressings with preparations of polyurethane foams in treating 129 patients with PrUs [20], found no significant between group difference (RR, 0.82; 95% CI, 0.57 to 1.17).

Most previous studies comparing polyurethane and hydrocolloid dressings have methodological shortcomings, reducing the value of their results and conclusions. These included small sample sizes, resulting in low statistical power, as well as a lack of patient follow up, absence of ITT analysis, different outcome measures, and the inclusion of various wound types and different PrU stages.

Furthermore, among the many types of PrU treatments and dressings currently in use are silicone hydrogels, hydrocellular polyurethanes and polyurethane foams, hydropolymeric silicone and foams, hydrocolloids, and antimicrobial bioactive collagen (collagenase). However the use of most is based on little scientific evidence [3].However, scientific evidence is required to optimize the treatment of PrU-II, and pressure ulcers in general.

This study has been designed to avoid the methodological problems encountered in other studies and to provide better evidence for optimal PrU-II treatment. Our protocol includes training sessions for nursing staff involved in the conduct of the trial, and standardizing data collection.

Identification of optimal dressings can improve patient quality of life and decrease treatment costs. It won’t be able to succeed unless we don’t stop and try to shed light on this health problem with the resources which are at our disposal and are recommended in the main GCP guidelines with little evidence about them.

## Abbreviations

PrU: Pressure ulcers; PrU-II: Stage II pressure ulcers; EPUAP: European pressure advisory panel; GCP: Good clinical practice guidelines; CT: Clinical trial; AE: Adverse events; ITT: Intention to treat analysis
